## Abstract

**Background:**

Early neurological deterioration (END) is a critical determinant influencing the short-term prognosis of acute ischemic stroke (AIS) patients and is associated with increased mortality rates among hospitalized individuals. AIS frequently coexists with coronary heart disease (CHD), complicating treatment and leading to more severe symptoms and worse outcomes. Shared risk factors between CHD and AIS, especially elevated low-density lipoprotein cholesterol (LDL-C), contribute to atherosclerosis and inflammation, which worsen brain tissue damage. Proprotein convertase subtilisin/kexin type 9 (PCSK9) inhibitors offer a promising treatment option. They effectively lower LDL-C levels and may help reduce END in AIS patients with CHD. This study aims to evaluate how effective PCSK9 inhibitors are in reducing END among this high-risk group and to provide new insights for treatment strategies.

**Methods:**

This is a prospective, randomized, parallel-group, blinded-endpoint, single-center clinical study. A total of 156 AIS patients with a history of CHD and within 24 h from symptom onset will be recruited and randomized in a 1:1 allocation to either the PCSK9 inhibitor combined with statin treatment group (PI group) or the statin monotherapy group (AT group). The PI group will receive a combination therapy consisting of evolocumab and rosuvastatin calcium tablets, while the AT group will receive only oral rosuvastatin calcium tablets. The trial duration will last for 90 days and comprise three phases: screening, treatment intervention, and follow-up assessments. Participants will undergo comprehensive examinations and assessments on days 1, 7, 30, and 90 after enrollment.

**Discussion:**

This study aims to investigate the potential preventive effects of PCSK9 inhibitors on END in AIS patients with a history of CHD. A positive outcome from this trial could provide novel clinical strategies for reducing the incidence of END and improving the short-term prognosis among these stroke patients.

**Trial registration:**

China Clinical Trial Registry, ChiCTR2300078198. Registered on 30 November 2023.

**Supplementary Information:**

The online version contains supplementary material available at 10.1186/s13063-024-08709-2.

## Introduction

### Background and rationale {6a}

Early neurological deterioration (END) is defined as the progressive or stepwise exacerbation of neurological deficits within 7 days after onset of stroke, with an incidence ranging from 5 to 40% [1–4]. END is a crucial factor in determining short-term prognosis in patients with acute ischemic stroke (AIS); furthermore, it is associated with increased mortality rates among hospitalized individuals [5]. Given the significant clinical implications of END, preventing its occurrence is of paramount importance.

AIS and coronary heart disease (CHD) are leading causes of death worldwide, significantly impacting patients’ quality of life and prognosis while also placing a substantial burden on healthcare systems [6, 7]. Notably, in clinical practice, AIS often coexists with CHD, leading to more severe symptoms, higher mortality risks, and poorer prognoses compared to patients without CHD [8, 9]. However, the best treatment plan for these patients is still uncertain.

CHD and large artery atherosclerotic stroke share common risk factors. Elevated low-density lipoprotein cholesterol (LDL-C) leads to atherosclerosis [3]. In AIS, high levels of oxidized low-density lipoprotein (ox-LDL) activate pro-inflammatory signaling pathways in the affected area. This activation triggers the release of pro-inflammatory cytokines, including interleukin 6 (IL-6), interleukin 8 (IL-8), and tumor necrosis factor alpha (TNF-α) [10]. These cytokines worsen brain tissue damage in the ischemic penumbra [11]. Ox-LDL activation also raises the levels of matrix metalloproteinases (MMPs), which promote plaque instability [12, 13]. Detachment of unstable plaques and local thrombus accumulation that block distal blood vessels are key mechanisms of END in AIS [14]. According to the “Shanghai Expert Consensus on Enhanced Blood Lipid Management in Ischemic Stroke,” achieving LDL-C targets in AIS patients can reduce the risk of secondary early neurological deterioration (END) events and other vascular recurrences Tables 1 and 2.

**Table 1 Tab1:** Inclusion and exclusion criteria

Inclusion Criteria	1.Age between 18 and 80 years. 2.Acute ischemic stroke patients within 24 hours of onset. 3.Documented history of atherosclerotic coronary artery disease. 4.First-time onset or recurrent patients without residual sequelae such as limb paralysis affecting the current NIHSS score; previous mRS score ≤1. 5.Voluntary signing of informed consent.
Exclusion Criteria	1.Hemorrhagic or mixed-type stroke. 2.Patients with cerebral arteriovenous malformations or intracranial tumors. 3.Inability to control severe hypertension (systolic blood pressure persistently ≥180 mmHg or diastolic blood pressure ≥110 mmHg after active treatment), severe infections (meeting criteria such as elevated body temperature ≥38°C, signs of shock, infection-related consciousness impairment, respiratory failure, and blood gas analysis PO_2_ <60 mmH_2_O), or abnormal liver function (ALT > 100 IU/L or AST > 80 IU/L), renal dysfunction (glomerular filtration rate < 30 ml/min), or patients with bleeding tendencies in the blood system (platelets < 60×10^9^/L or APTT > 60 seconds or INR > 3). 4.History of previous cerebral hemorrhage. 5.Occurrence of retinal or visceral bleeding within 30 days. 6.Use of PCSK9 inhibitors in the three months preceding the onset. 7.Patients with impaired consciousness. 8.Known allergy or intolerance to PCSK9 inhibitors or statin components. 9.Pregnant or lactating women and those planning pregnancy within six months. 10.Participants deemed unsuitable for the trial by the investigator.

*NIHSS* National Institutes of Health Stroke Scale, *mRS* Modified Rankin Scale, *ALT* Alanine Aminotransferase, *AST* Aspartate Aminotransferase, *APTT* Activated Partial Thromboplastin Time, *INR* International Normalized Ratio

**Table 2 Tab2:** Trial registration data

Data category	Information
Primary registry and trial identifying number	China Clinical Trial Registry ChiCTR2300078198
Date of registration in primary registry	30 November, 2023
Public title	PCSK9 Inhibitor Prevents Early Neurological Deterioration in Acute Ischemic Stroke Patients with a History of Coronary Heart Disease: A Clinical Trail
Scientific title	PCSK9 Inhibitor Prevents Early Neurological Deterioration in Acute Ischemic Stroke Patients with a History of Coronary Heart Disease: A Clinical Trail
Study leader	[name]
Primary sponsor	First Affiliated Hospital of Dalian Medical University
Secondary sponsor	First Affiliated Hospital of Dalian Medical University
Source(s) of funding	None
Study type	Interventional study Allocation: randomized intervention model
Countries of recruitment	China
Intervention(s)	PI group: Subcutaneous injection of evolocumab 140mg every two weeks, combined with oral administration of rosuvastatin 20mg once nightly.
	AT group: oral administration of rosuvastatin 20mg once nightly
Key inclusion and exclusion criteria	Ages eligible for study: between 18 and 80 years Sexes eligible for study: both Accepts healthy volunteers: no
	Inclusion criteria: Acute ischemic stroke patients with a History of Coronary Heart Disease within 24 hours of onset
	Exclusion criteria: Hemorrhagic or mixed-type stroke. Cerebral arteriovenous malformations or intracranial tumors. Uncontrolled severe hypertension. History of previous cerebral hemorrhage. Retinal or visceral bleeding within 30 days. Use of PCSK9 inhibitors in the past three months. Impaired consciousness. Known allergy or intolerance to PCSK9 inhibitors or statin components. Pregnancy, lactation, or planning pregnancy within six months. Deemed unsuitable for the trial by the investigator.
Date of first enrolment	1 December, 2023
Target sample size	156
Recruitment status	Recruiting
Primary outcome(s)	END and severe END
Key secondary outcomes	Rate of good prognosis at 30 and 90 days. Recurrence rate of symptomatic cardiovascular and cerebrovascular events within 90 days. Changes in blood biochemical indices and inflammatory factors.

In this context, proprotein convertase subtilisin/kexin type 9 (PCSK9) inhibitors, a novel and potent class of lipid-lowering drugs, are gaining significant recognition. By competitively inhibiting the binding of PCSK9 to low-density lipoprotein receptors (LDLR), they reduce LDLR degradation effectively [15], thus lowering circulating low-density lipoprotein cholesterol (LDL-C) levels. Studies have demonstrated that PCSK9 inhibitors can suppress pro-inflammatory cytokines release [10], reduce endothelial cell apoptosis [16], and inhibit platelet activation [17]. As a result, these inhibitors hold promise in preventing atherosclerosis progression and reducing cardiovascular events. This study aims to assess the effectiveness of PCSK9 inhibitors in lowering the incidence of END among AIS patients with a history of CHD.

The findings of this study will not only elucidate the potential role of PCSK9 inhibitors in AIS patients with a history of CHD but also provide novel insights and directions for the treatment of this specific patient population.

### Objectives {7}

The primary objective of this study is to investigate the effects of PCSK9 inhibitors on END in AIS patients with a history of CHD within 24 h of symptom onset. Secondary objectives include evaluating changes in daily living abilities, recurrence rates of cardiovascular and cerebrovascular events within 90 days, alterations in blood biochemical indices/markers, and variations in inflammatory factors between the two patient groups after treatment.

### Trial design {8}

This is a prospective, randomized, parallel-group, blinded-endpoint, single-center clinical study aimed at investigating the preventive effects of PCSK9 inhibitors on END in patients with AIS and a history of CHD within 24 h of symptom onset. The study will be conducted from December 2023 to November 2025 at the Neurology Department of the First Affiliated Hospital of Dalian Medical University. A total of 156 AIS patients with a history of CHD and symptom onset within 24 h will be recruited and randomly assigned to either the PCSK9 inhibitor combined with statin treatment group (PI group) or the statin monotherapy group (AT group). The PI group will receive a combination therapy consisting of evolocumab and rosuvastatin calcium tablets, while the AT group will receive only oral rosuvastatin calcium tablets alone. The trial duration will be 90 days and consist of three phases: screening, treatment, and follow-up. Participants will undergo examinations and assessments on days 1, 7, 30, and 90 after enrollment. Written informed consent is mandatory for all participants prior to trial entry. The flow chart of the trial is illustrated in Fig. 1.

**Fig. 1 Fig1:**
[figure not shown]
Expected trial plan. Not included in the diagram are participants who are excluded or stop participation at any time for various reasons

## Methods: participants, interventions, and outcomes

### Study setting {9}

The study will be conducted at the First Affiliated Hospital of Dalian Medical University, located in Dalian, China. This hospital will serve as the primary site for the recruitment of participants and the implementation of the clinical trial. The anticipated duration of the study is 2 years, encompassing participant enrollment, intervention administration, assessments, and data analysis.

### Eligibility criteria {10}

Participants will be recruited from the Neurology Department of the First Affiliated Hospital of Dalian Medical University based on predefined inclusion criteria. Only eligible individuals will be invited to enroll in the study.

The inclusion criteria are as follows:Age between 18 and 80 yearsAcute ischemic stroke patients within 24 h of onsetDocumented history of atherosclerotic coronary artery diseaseFirst-time onset or recurrent patients without residual sequelae such as limb paralysis affecting the current NIHSS score; previous mRS score ≤ 1Voluntary signing of informed consent

The exclusion criteria are as follows:Hemorrhagic or mixed-type strokePatients with cerebral arteriovenous malformations or intracranial tumorsInability to control severe hypertension (systolic blood pressure persistently ≥ 180 mmHg or diastolic blood pressure ≥ 110 mmHg after active treatment), severe infections (meeting criteria such as elevated body temperature ≥ 38 °C, signs of shock, infection-related consciousness impairment, respiratory failure, and blood gas analysis PO_2_ < 60 mmH_2_O), or abnormal liver function (ALT > 100 IU/L or AST > 80 IU/L), renal dysfunction (glomerular filtration rate < 30 ml/min), or patients with bleeding tendencies in the blood system (platelets < 60 × 10.^9^/L or APTT > 60 s or INR > 3)History of previous cerebral hemorrhageOccurrence of retinal or visceral bleeding within 30 daysUse of PCSK9 inhibitors in the three months preceding the onsetPatients with impaired consciousnessKnown allergy or intolerance to PCSK9 inhibitors or statin componentsPregnant or lactating women and those planning pregnancy within 6 monthsParticipants deemed unsuitable for the trial by the investigator

### Who will take informed consent? {26a}

All eligible participants will be invited to participate in this study. Two trained research personnel will conduct face-to-face sessions with potential participants or their authorized surrogates, wherein they will provide comprehensive explanations regarding the study’s objectives, procedures, associated risks, and the rights of participants. They will address any queries from participants or surrogates and ensure a thorough comprehension of the provided information. Prior to enrollment, informed consent will be obtained through signed written consent forms from either the participant or their authorized surrogate.

### Additional consent provisions for collection and use of participant data and biological specimens {26b}

The consent form requests participants’ permission for the continued use of their data even in the event of trial withdrawal. Additionally, participants are requested to grant permission to the research team for sharing pertinent data with applicable regulatory authorities. It is noteworthy that the trial does not encompass the collection of biological specimens.

## Interventions

### Explanation for the choice of comparators {6b}

The selection of comparators in this study is based on the current standard treatment for AIS. Intensified lipid-lowering therapy with statins represents the established treatment regimen for AIS patients with a history of coronary heart disease (CHD). Therefore, comparing PCSK9 inhibitor combined with statin treatment to statin monotherapy aims to evaluate the additional benefits of PCSK9 inhibitors in preventing END in AIS patients with a history of CHD.

### Intervention description {11a}

After signing the informed consent, participants will be randomly allocated to either the PI group (intervention group) or the AT group (control group). Participants in the PI group will receive a subcutaneous injection of 140 mg (1 ml) of evolocumab (Rephatha®, Amgen Inc.) and orally take 20 mg of rosuvastatin (Crestor®, AstraZeneca Inc.) calcium tablets within 1 h of randomization. Starting from the following day, they will receive 20 mg of rosuvastatin calcium tablets orally every evening and 140 mg of evolocumab subcutaneously once every 2 weeks. Participants in the AT group will receive 20 mg of rosuvastatin calcium tablets orally within 1 h of randomization. Starting from the next day, they will continue to orally receive 20 mg of rosuvastatin calcium tablets orally every evening.

### Criteria for discontinuing or modifying allocated interventions {11b}

Participants are allowed to withdraw from the study at any time due to various reasons, including failure to meet the inclusion criteria, inability to continue with the intervention treatment, or participant request.

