### Concealment mechanism {16b}

The allocation sequence will be concealed using sequentially numbered, opaque, sealed envelopes. An independent researcher, not involved in recruitment, treatment, or assessment, will prepare these envelopes, each containing the group assignment (either the AT group or the PI group). After obtaining informed consent and completing baseline measurements, participants will be assigned the next sequential envelope by a designated researcher who is not involved in treatment or outcome assessment. The envelopes will remain sealed until the participant is assigned to an intervention, ensuring the allocation sequence is concealed from those enrolling participants and assigning interventions.

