## Assignment of interventions: blinding

### Who will be blinded {17a}

Researchers responsible for data collection and outcome analysis will be blinded to group assignments until after data analysis is completed, as they will not be involved in participant assignment or intervention implementation.

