### Procedure for unblinding if needed {17b}

Not applicable to study; the design is open label, so unblinding will not occur.

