## Statistical methods

### Statistical methods for primary and secondary outcomes {20a}

Once all participants have completed their assessments, data analysis will commence. To reduce bias, the data analyst will remain blinded during the analysis process. Only participants who strictly adhere to the intervention protocol will be included in the analysis. Data that are missing or deviate from the protocol will be excluded from the analysis.

The primary and secondary outcomes will be combined as dependent variables in the generalized linear model (GLM). First, a univariate analysis of the treatment groups will be performed to determine the unadjusted risk ratio (RR) and odds ratio (OR), along with a 95% confidence interval (CI). Next, continuous variables like the NIHSS score at admission, mRS score, and age will serve as covariates. Categorical variables such as sex, hypertension, diabetes, and prior strokes will be included as factors in the GLM to reduce variance error. If the outcomes show statistical significance for the main effects, interaction effects will be used to assess differences between the groups. Changes in blood biochemical indices will be analyzed using repeated measures ANOVA or mixed-effects models, accounting for measurements taken at baseline, 7 days, 30 days, and 90 days. Changes in inflammatory factors (IL-6, IL-8, TNF-α) from baseline to 7 days will be evaluated using paired *t*-tests or Wilcoxon signed-rank tests, based on data distribution. Sensitivity analysis will use the criterion for severe END, defined as either a 4-point increase in NIHSS or a 2-point worsening in motor function based on a higher threshold. All analyses will be conducted using SPSS (IBM Corp., Armonk, NY, USA), with a significance threshold of *α* = 0.05.

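### Item 11b permits allocated participants to leave the study for ineligibility, so some may go without an END value for reasons tied to arm and early course

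*Protocol article*

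**What the plan says.** Item 11b, headed "Criteria for discontinuing or modifying allocated interventions {11b}", lets participants withdraw at any time "due to various reasons, including failure to meet the inclusion criteria". What is left is the study, not only the treatment.

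The surrounding sections fix the timing and the consequences:

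- **Allocation (16b).** "After obtaining informed consent and completing baseline measurements, participants will be assigned the next sequential envelope". Eligibility should therefore be known before the arm is.
- **First treatment (11a).** Both arms start within an hour of randomisation. For the control arm: "Participants in the AT group will receive 20 mg of rosuvastatin calcium tablets orally within 1 h of randomization".
- **Blinding (17a, 17b).** "Researchers responsible for data collection and outcome analysis will be blinded to group assignments until after data analysis is completed", but "the design is open label, so unblinding will not occur".
- **Primary outcome (Outcomes; Treatment).** END covers 24 h to 7 days after onset and is evaluated at the day 7 visit.
- **Analysis (20a).** Only strict adherers are analysed, and "Data that are missing or deviate from the protocol will be excluded from the analysis".
- **Analysis (20c).** The primary outcome uses all randomised participants with at least one treatment record. Multiple imputation applies only if more than 10% of data are missing.
- **Consent (26b).** Permission is sought to go on using data after withdrawal.

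**The concern.** A randomised comparison is protected by following everyone who was randomised, whatever is later learned about their eligibility. Item 11b opens a way out for participants who already have an allocation, on a ground that staff may come to judge after seeing the arm and the first days of the illness.

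Several inclusion criteria can be looked at again later: whether the event was an ischaemic stroke, whether onset was within 24 h, whether the coronary disease is documented as atherosclerotic, and whether old sequelae affect the NIHSS. A patient who worsens is a plausible candidate for that second look. No section requires the second look to be blind to arm or limited to information from before randomisation.

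At stake is the primary comparison. If removal is related to both arm and course, the END rates are no longer compared between the groups that randomisation formed.

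**Working it through.** **1. The plan's own figure.** Inputs from Sample size: END 33.3% (control) and 13.6% (evolocumab), two-sided alpha 0.05, power 80%, 70 per group, 10% loss.

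- Printed formula, with the mean rate p = (0.333 + 0.136)/2 = 0.2345 and δ = 0.197: n = 2 × (1.96 + 0.84)² × 0.2345 × 0.7655 / 0.197² = 72.5 per group.
- Unpooled variance: 68.6 per group. The stated 70 lies between the two and has power of about 0.79.
- Loss: 70/0.90 = 77.8, so 78 per group and 156 in total, as stated.

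The sample size is not affected by this point. It supplies the scale: the plan allows for 78 − 70 = 8 losses per group.

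**2. What happens to a participant withdrawn under 11b before day 7.**

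| Rule | Effect on the primary outcome |
|---|---|
| 11b | The participant may leave the study; no later assessment is provided for |
| 26b | Data already collected may be used; a day 7 score not yet taken is not supplied |
| 20c | The participant stays in the set if treated, but without an END value |
| 20c, imputation | Starts above 10% missing. If counted over all 156, that is more than 15.6, so 16 or more |
| 20a | Missing data are excluded; deviating data too, so a recorded END value could also go |

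A handful of such losses stays below the imputation threshold. Under either analysis section, those participants would contribute nothing to the END comparison.

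**3. How much selective loss could do.** The documents give no rate of late-found ineligibility, so this is an illustration. Assumptions: no true effect, END 33.3% in both arms, 78 per arm, and k evolocumab participants with END removed (the worst case). The observed evolocumab rate at the expected count is (26 − k)/(78 − k). The rejection rate is for the pooled two-proportion z test at |z| > 1.96, by simulation.

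| k | Evolocumab END rate | Risk ratio | Two-sided rejection |
|---|---|---|---|
| 0 | 33.3% | 1.00 | 5.2% |
| 2 | 31.6% | 0.95 | 6.0% |
| 4 | 29.7% | 0.89 | 8.5% |
| 6 | 27.8% | 0.83 | 12.6% |
| 8 | 25.7% | 0.77 | 19.4% |

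Even k = 8 is below the 16 missing at which imputation would begin. If removal were unrelated to arm and outcome there would be no bias, only lower precision: power of about 0.83 at 78 per arm and 0.79 at 70.

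**The case against.** The other side has good points, and they limit how far this goes.

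- **Permission, not exclusion.** A reader might infer that 11b orders ineligible participants to be removed, or that the ground can operate only after allocation. The text supports neither. It says participants may withdraw, and a study with a screening phase could use the same words for ordinary screen failure. The heading favours the post-allocation reading but does not exclude the other.
- **END is not always lost.** A reader might infer that everyone withdrawn this way lacks a day 7 score. Withdrawal can come at any time in 90 days, and after day 7 the primary outcome is already known. Worsening seen before withdrawal may also be on record, with permission sought for its use. What stands is that an evaluation still to come is not provided for.
- **20a does not simply prevail.** A reader might infer that the exclusion rule overrides the intention-to-treat definition. The two conflict and the article does not say which governs. Part of the harm belongs to that conflict, but settling it in favour of 20c would still leave unobserved values unobserved.
- **Boundary examples prove little.** A reader might infer that one or two removals would usually turn the result. In chosen cases they do: 24/78 against 15/78 gives p = 0.096, and 24/78 against 13/76 gives 0.047; 22/78 against 12/78 gives 0.052, and 22/78 against 11/77 gives 0.034 (chi-square, uncorrected). With continuity correction the two smaller values become 0.073 and 0.055. Near the planned rates, 26/78 against 11/78 gives 0.005, and removing two evolocumab events leaves the conclusion unchanged.
- **Condensed article.** Follow-up of late-found ineligible participants may be set out in the full protocol. That would excuse silence, but here the article states a ground for leaving, and that ground should change.

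**Conclusion.** The point holds in a limited form. Read under its heading, item 11b permits study withdrawal for ineligibility found after randomisation, at a time when the treating team knows the arm. Neither analysis section recovers an END value that was never taken. The loss can therefore depend on arm and early course.

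The size cannot be derived, because the frequency of late-found ineligibility is unknown. A few selective losses would matter mainly if the result lies near the threshold, and larger numbers would do real damage only if nearly all were selective in the same direction. The conclusion rests on three assumptions: that the heading governs the sentence, that treating staff can influence such withdrawals, and that no follow-up of these participants is arranged elsewhere. The documents do not show that such withdrawals will happen or that the result will be biased. The change is worth making because it is simple and the weakness lies in the primary comparison.

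**What to change.** - **Item 11b.** Remove not meeting the inclusion criteria as a ground for leaving the study after randomisation. Screen failure before randomisation is unaffected. State that ineligibility found later is recorded as a protocol deviation, and that the day 7, 30 and 90 outcome assessments continue unless the participant withdraws consent.
- **Items 20a and 20c.** Reconcile them so that the primary outcome is analysed in the assigned arm, including participants later found ineligible. They may be left out only in a supportive analysis, with ineligibility judged from pre-randomisation data by someone unaware of arm and outcome.

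The cost is about one sentence in 11b and one in 20c, plus the alignment of 20a. The visits are already scheduled. The downside is slight dilution of the effect by a few ineligible participants. No treatment rule is implied: whether study treatment continues in such a participant is a separate matter.
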